Antibiotic overprescribing for infectious diseases is high in nursing homes. In a recent project on the prevalence of antimicrobial agents in 3052 long-term care facilities in 24 European Union countries in 2016-2017, 4.9% of the residents had received at least 1 antimicrobial agent on the day of the survey [13]. This study also showed that for a 1% increase in the proportion of residents older than 85 years, the prevalence of antimicrobial use increased by 5%. In addition, approximately 30% of the antibiotics prescribed were given prophylactically, and most were given inappropriately, with a wide variation across European countries. Furthermore, the urinary tract was the most common body site for which antimicrobials are prescribed, with nearly 50% of the cases, and according to the authors, at least 60% of these antimicrobials prescribed for UTI were inappropriate, leading to a spread of multidrug-resistant uropathogens [13]. As a result, Watch and Reserve broad-spectrum antibiotics, as defined by the World Health Organization Access, Watch, Reserve classification [14], are commonly given to residents with these infections, perpetuating the problem of antimicrobial resistance (AMR), which is accompanied with higher morbidity, mortality, health, and intersectoral and societal costs [15].

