### Aims

The primary objectives of this study (IMAGINE project) are aimed at increasing the IPC elements implemented by 50% and decreasing the incidence of inappropriate antibiotic consumption for UTIs by 40%, with a subsequent 20% reduction in the incidence of UTIs. Different secondary objectives are planned: (1) reduction in inappropriate use of urinary catheters in nursing home residents; (2) reduction in the percentage of inappropriate antibiotic use for the prophylaxis of UTIs; (3) reduction in the number of Watch and Reserve antibiotics from the World Health Organization Access, Watch, Reserve classification; (4) improvement in the satisfaction of nursing home HCPs, residents, and relatives; (5) reduction in the incidence of health care–associated infections treated with antibiotics others than UTI; and (6) reduction in the percentage of hospital admissions.

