### Data Analysis Plan

The data collected in the specific registration charts have a primary function at the individual level of health professionals, that is, helping them to improve their practice by reconsidering their treatment choices considering clinical evidence, guidelines, and professional consensus [31]. The second function is to analyze the data to evaluate the effect of the intervention. In each audit, data are recorded for all antibiotics prescribed during the 3-month period. We aim to record a minimum of 50 cases in each of the nursing homes recruited (at least 100 nursing homes), yielding an approximate number of 5000 cases in each registration period.

We will apply the chi-square test to determine the frequencies and appropriateness of prescriptions before and after the intervention and Student *t* test for the number of hygiene elements implemented in the nursing homes to test the null hypothesis of no effect of the interventions. To measure the potential reduction in UTIs, we will assume that antibiotics are always prescribed for these infections and every antibiotic is associated with a new episode of UTI [32]. The number of hygiene elements implemented will be compared with a threshold that will be defined during the participatory action research analysis. The appropriateness of antibiotic prescriptions will be defined according to an algorithm based on symptoms and patient characteristics that will be developed at the start of the project. We will also estimate the effect of the interventions on inappropriate prescriptions for UTIs using multilevel logistic regression models with 2 levels: cases and HCP participants, to allow for the fact that patients belonging to the same HCP are not independent of each other [33]. Statistical significance will be considered with *P*<.05. The data will be analyzed using the current version of the Stata statistical program (version 18, StataCorp LLC).

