### Ethical Considerations

The study is conducted in accordance with the protocol, the Declaration of Helsinki, the principles of Good Clinical Practice, The General Data Protection Regulation (of the European Union) 2016/679 and the Human Research Act as well as other locally relevant regulations. Appropriate regulatory or ethical approval has been sought in each of the countries taking part in the study, and all study procedures started after gaining approval on the basis of the master protocol, translated where necessary to local language. In Spain, the coordinating country, the study protocol was approved by the Ethics Committee of Institut Universitari d’Investigació en Atenció Primària (IDIAP Jordi Gol), Institute of Research in Primary Health Care (23/080-P).

Nursing homes have been contacted by local coordinators that have explained the study and handed over the information, giving the nursing home time to read it and ask any questions. Informed consent was obtained from all participants. HCPs are participating voluntarily in this quality improvement project. No personnel data are collected from either HCPs or patients. A nursing home can withdraw from the project at any time without giving any explanation. The information gathered from the residents’ prescriptions are personally nonidentifiable data and we are collecting the minimum data set necessary for the study. Data are anonymized from the beginning, coded in the template with the code of the nursing home and a consecutive number for each antibiotic treatment. Individual patient consent is therefore not required.

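### UTI incidence is counted as UTI antibiotic courses, so an inappropriate course withheld registers as a UTI prevented; if about half or more of courses are inappropriate, this alone could meet the 20% target

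*Protocol article*

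**What the plan says.** The Aims section places two linked targets under the primary objectives: "decreasing the incidence of inappropriate antibiotic consumption for UTIs by 40%, with a subsequent 20% reduction in the incidence of UTIs". A third target concerns the number of infection-control elements and is not at issue here.

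The Data Analysis Plan gives one rule for the UTI target: "we will assume that antibiotics are always prescribed for these infections and every antibiotic is associated with a new episode of UTI". It also says "In each audit, data are recorded for all antibiotics prescribed during the 3-month period", so a case enters the data only if an antibiotic was given. Appropriateness will be judged by "an algorithm based on symptoms and patient characteristics that will be developed at the start of the project".

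The Introduction reports from a European survey that "at least 60% of these antimicrobials prescribed for UTI were inappropriate", and it attributes much antibiotic overuse to overdiagnosis. The Discussion adds asymptomatic bacteriuria and non-specific symptoms as causes, and it describes training that concentrates on when a UTI should be suspected.

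**The concern.** By the protocol's own account, many antibiotics labelled as UTI treatment go to residents who do not have a UTI, and the intervention is built to stop those courses. Under the counting rule each of them was a UTI in the first audit and is absent in the second. The quantity called UTI incidence therefore contains the courses that the 40% target removes.

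The rule also needs the link between infection and prescription to be the same in both audits. The intervention is meant to change that link.

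At stake is the meaning of a primary objective. A fall in the count could be reported as infections prevented when part or all of it is a change in prescribing. The reverse can also happen: genuine prevention can be diluted by inappropriate courses that do not change.

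**Working it through.** **The plan's own figure.** The only size given is about 5000 cases per audit: 50 cases × 100 homes = 5000, which reproduces. It does not enter the argument below, which is about bias.

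**Inputs**
- Target cut in inappropriate UTI antibiotics: 40% (Aims).
- Target fall in UTI incidence: 20% (Aims).
- Counting rule: one UTI antibiotic = one new UTI (Data Analysis Plan).
- *s*, the baseline share of UTI courses that are inappropriate: not given for this study, so varied. The Introduction's survey figure is at least 60%.
- *f*, the fraction of removed inappropriate courses replaced by an appropriate antibiotic: not given, so varied.

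**Step 1. No infection prevented, all removed courses withheld (*f* = 0).** Fall in counted UTIs = *s* × 0.40.

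| Assumed *s* | Fall in counted UTIs |
|---|---|
| 30% | 0.30 × 0.40 = 12% |
| 40% | 0.40 × 0.40 = 16% |
| 50% | 0.50 × 0.40 = 20% |
| 60% | 0.60 × 0.40 = 24% |
| 70% | 0.70 × 0.40 = 28% |

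Break-even with the 20% target: *s* = 0.20 / 0.40 = 50%.

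**Step 2. Some removed courses are replaced.** Fall = *s* × 0.40 × (1 − *f*). At *s* = 60%:

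| *f* | Fall in counted UTIs |
|---|---|
| 0 | 24% |
| 10% | 21.6% |
| 25% | 18% |
| 50% | 12% |
| 100% | 0% |

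Break-even: 1 − *f* = 0.20 / 0.24, so *f* ≈ 16.7%.

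**Step 3. The other reading of the 40% target.** The Aims speak of the incidence of inappropriate consumption, which is the reading used above. The end of the Introduction speaks of a percentage. If the percentage inappropriate falls by 40% and appropriate courses stay constant, the count becomes (1 − *s*) / (1 − 0.6*s*) of baseline. The fall is then 14.6% at *s* = 30%, 21.1% at 40%, 28.6% at 50% and 37.5% at 60%, with break-even at 0.20 / 0.52 ≈ 38.5%. The artefact is larger on this reading.

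**Step 4. Both targets met exactly at *s* = 60%.** Per 100 baseline courses, inappropriate courses go from 60 to 60 × 0.60 = 36 and the total goes to 80. Appropriate courses go from 40 to 80 − 36 = 44, a rise of 10%. Reported success on both targets would then accompany more appropriately treated UTIs.

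**Step 5. The reverse case at *s* = 60%.** A real 20% fall in appropriately treated UTIs, with inappropriate courses unchanged, shows as 0.40 × 0.20 = 8%.

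**The case against.** The strongest points on the other side are these.

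- **The assumption is declared and carries a citation, and the text speaks of a potential reduction.** That is true. But the Discussion still expects a lower UTI incidence to be seen in the second audit, and disclosure does not make the assumption stable across an intervention that changes when antibiotics are given.
- **The Discussion already covers diagnostic misclassification.** It argues that the bias acts before and after alike and so hardly touches the effect. That requires equal misclassification in both audits, which training on when to suspect a UTI is meant to alter. The argument does not answer the point.
- **The 60% is not this study's figure.** This stands. It comes from an outside survey, and the study's share depends on an algorithm and a baseline audit that are not shown. If the algorithm also faults drug choice, switching drugs would leave the count unchanged. The stated basis, symptoms and patient characteristics, makes that less likely but does not exclude it.
- **Inappropriate courses may be replaced rather than withheld.** This stands, and Step 2 shows its effect.

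A reader might go further than the documents allow in three ways:

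- *That meeting the 40% target necessarily produces the 20% fall.* It does so only under the conditions in Steps 1 to 3.
- *That prophylactic courses and second courses within an episode are certainly counted as UTIs.* The registration chart and the instruction sheet with the inclusion criteria are not shown. The statement that "approximately 30% of the antibiotics prescribed were given prophylactically" refers to all antibiotics, so it does not size this problem.
- *That the study cannot address UTI reduction at all.* Symptoms are on the chart and an appropriateness algorithm is planned, so the useful split can be made. The fault lies in the counting rule and the label.

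**Conclusion.** The concern holds in conditional form. As defined, the UTI measure is a count of UTI antibiotic courses and cannot tell prevention from prescribing change. If the 40% target is met by withholding courses and no infection is prevented, the spurious fall is 12% to 24% for inappropriate shares of 30% to 60%. It reaches the full 20% target only if the share is at least 50% and, at a 60% share, no more than about 17% of removed courses are replaced. Below those limits the bias is smaller but still favours a reduction, unless every removed course is replaced.

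This rests on reading the 40% as a cut in the number of inappropriate courses, and on inappropriate meaning mainly that UTI criteria were not met. Because the affected claim sits under the primary objectives, the rule should be changed before the two audits are compared.

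**What to change.** 1. Rename the count of all UTI-labelled courses 'antibiotic courses for UTI', and do not report it as UTI incidence.
2. Base any statement about UTI reduction on treated courses that meet the symptom criteria of the study's own algorithm, fixed once and applied identically to both audits.
3. Show the total change split into algorithm-positive and algorithm-negative courses.
4. Exclude prophylactic courses where the chart identifies them.

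**Cost.** A change of wording and a derived variable from symptoms already on the chart, with no new data collection. There will be fewer events and probably a smaller headline reduction.

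**Limits to state.** The revised measure should not be presented as simply conservative:
- Untreated UTIs are not registered, so symptomatic episodes left untreated after training would still look prevented. This biases towards a reduction.
- Staff may record symptoms differently after training, which may bias in the other direction.
- Records are "coded in the template with the code of the nursing home and a consecutive number for each antibiotic treatment", so repeat courses within one episode may not be identifiable. Linking courses to episodes should not be promised unless the chart supports it.

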### Setting

We are carrying out interventions in nursing homes in 8 European countries: Denmark, Greece, Hungary, Lithuania, Poland, Slovakia, Slovenia, and Spain. In each country, at least 10 nursing homes participate and a team of 4 HCPs in each nursing home are actively involved. Different types of professionals are involved in the health care of residents in the nursing homes: registered nurses, doctors that can be external or working in the facility part-time, health care assistants, or health care helpers. The participating nursing homes select the HCPs of their setting who actively take part in the study. These HCPs will, in turn, become trainers in their own nursing home after the intervention meetings.

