### Data Management

The collection of the audit data is performed on paper. The registration templates will be stored securely in in each participating nursing home and will be accessible only by study staff and authorized personnel. Charts will be transferred electronically to the Audit Project Odense service provider to be entered in a database [31]. Data from residents will be anonymously collected from the beginning and no identifiable or personal information will be gathered. Nursing homes will be identified by a code. Qualitative interviews will be audio recorded, transcribed, and translated, and any identifiable information will be deleted in the process. Translations will be transferred securely to the organization in charge of analyzing the results. Anonymized data from the survey will be stored for a minimum of 5 years after publication of the results. Anonymized project data will be shared for common analyses and presentation to the scientific community through publications and conferences.

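### The multilevel model clusters on the HCP, but the records are described as carrying only a nursing-home code, and the model has no nursing-home level

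*Protocol article*

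**What the plan says.** The Data Analysis Plan (Methods) sets a chi-square test for appropriateness of prescriptions before and after the intervention. It adds an estimate of the effect on inappropriate UTI prescriptions from "multilevel logistic regression models with 2 levels: cases and HCP participants". The stated reason is "to allow for the fact that patients belonging to the same HCP are not independent of each other".

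Two other sections describe the identifiers:

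- Data Management: "Nursing homes will be identified by a code".
- Ethical Considerations: records are "coded in the template with the code of the nursing home and a consecutive number for each antibiotic treatment", and "No personnel data are collected from either HCPs or patients".

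Under Setting, "a team of 4 HCPs in each nursing home are actively involved", and these staff are drawn from "registered nurses, doctors that can be external or working in the facility part-time, health care assistants, or health care helpers". Those who attend the training then train their own home. Under Data Collection, the chart is meant to capture every antibiotic prescription made in the home. The planned volume is at least 50 cases in each of at least 100 homes, about 5000 per audit.

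**The concern.** There are two separate problems.

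1. **The level-2 unit is not among the described identifiers.** The model groups cases by HCP. The article names a home code and a running treatment number, and nothing that says which of the four HCPs a case belongs to or which HCP in 2025 is the same person as in 2024. An analysis plan would not simply fill this in: the article states both the model level and the record coding, and the two do not match.

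2. **The nursing home is absent from the model.** Four HCPs in one home share residents, routines and the onward training, and a case need not belong to a single registering HCP, since the team may include assistants and helpers and the doctor can be external. If a home improves or worsens as a whole between audits, its four HCPs move together. A model with an HCP intercept alone counts them as four independent pieces of evidence on the change.

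Reducing inappropriate antibiotic use for UTIs is a primary objective (Aims). The chi-square test makes no allowance for clustering, so this model is the only stated protection against dependence for that objective.

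**Working it through.** **Step 1. The plan's own figure.** 50 cases × 100 homes = 5000 per audit, as stated. With 4 HCPs per home this is 400 HCPs and 50/4 = 12.5 cases each per audit, if cases could be linked to an HCP. The article gives no power calculation, intracluster correlation or variance component, so every value below is an assumption chosen to show a range.

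**Step 2. The sections side by side.** Data Analysis Plan: level 2 is the HCP. Data Management: the coded unit is the nursing home. Ethical Considerations: the record holds a home code plus a consecutive treatment number. None of these sections describes an HCP code.

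**Step 3. HCP code exists and is linked across audits.** Linear approximation with H = 100 homes, K = 4 HCPs and m = 12 cases per HCP and period (12.5 rounded down), so K·m = 48 cases per home and period. Let s be the stable home variance, g the home-by-period variance and e = 1 − s − g the residual, all as shares of the total.

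- True variance of the before-after difference: 2e/(HKm) + 2g/H.
- Variance that the HCP-intercept model reports: about 2(e + g)/(HKm). The stable part s is absorbed by the intercept and g falls into the residual.
- Ratio: R = (e + 48g)/(e + g).
- Actual two-sided type I error at nominal 5%: 2[1 − Φ(1.96/√R)].

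| s | g | R | Type I error |
|---|---|---|---|
| 0.05 | 0 | 0.95/0.95 = 1.00 | 5.0% |
| 0.05 | 0.02 | (0.93 + 0.96)/0.95 = 1.99 | 16.5% |
| 0.10 | 0.02 | (0.88 + 0.96)/0.90 = 2.04 | 17.0% |
| 0.10 | 0.05 | (0.85 + 2.40)/0.90 = 3.61 | 30.2% |

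The stable variance s hardly matters; g drives the result.

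**Step 4. Fewer UTI cases.** The 50 cases are all antibiotics, while the model concerns UTIs. The Introduction puts the urinary tract at nearly half of antimicrobial prescriptions. Halving to 24 cases per home and period gives R = (0.93 + 0.48)/0.95 = 1.48, type I error 10.8%, for s = 0.05 and g = 0.02; and R = (0.85 + 1.20)/0.90 = 2.28, type I error 19.4%, for s = 0.10 and g = 0.05.

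**Step 5. HCP code exists but is not linked across audits.** HCP clusters are then specific to a period and absorb both s and g. Take total home variance s + g = 0.10 within a period, residual 0.90, between-period correlation c of the home effects, and m = 6.25 (25 UTI cases per home and period, 4 HCPs). Dropping the common factor 2/H:

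- Model variance: (0.10 + 0.90/6.25)/4 = 0.061.
- True variance: 0.90/(4 × 6.25) + 0.10(1 − c) = 0.036 + 0.10(1 − c).

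| c | R | Type I error |
|---|---|---|
| 1 | 0.036/0.061 = 0.59 | 1.1% |
| 0.8 | 0.056/0.061 = 0.92 | 4.1% |
| 0.5 | 0.086/0.061 = 1.41 | 9.9% |

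The test is conservative when homes are stable and too liberal when they drift apart. A binary simulation of the same setting (109 homes, 60% inappropriate, 3000 runs, errors clustered on HCP-by-period) gave about 1%, 5% and 8%.

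**The case against.** **An HCP code may exist.** The chart template (Figure 2) and the instruction sheet are not shown. The coding sentence explains why resident consent is not needed and is not offered as a full list of fields. The remark about personnel data reads like a slip for personal data, which would not exclude a pseudonymous HCP number. The Data Analysis Plan speaks of use by individual professionals, and the Discussion says the same participants are compared before and after. This stands. A reader might infer that the model cannot be fitted at all; the documents support only that it cannot be fitted on the identifiers they describe.

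**Stable home differences cancel.** The same homes are audited twice, so a persistently high- or low-prescribing home does little harm to the before-after contrast. This also stands. A reader might infer that the confidence intervals are bound to be too narrow; steps 3 and 5 show that this depends on home-by-period variation and on whether HCPs are linked.

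**A home intercept alone would not solve it.** An analysis stratified by home with one common change is also too liberal when homes drift, so inflation of that kind measures a missing home-by-period term and not the choice of HCP over home. That is correct, and it is why the remedy needs more than relabelling level 2.

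**The model is supplementary, and article readers should expect detail elsewhere.** The chi-square test comes first and the model is an addition. That lowers the severity. It does not remove the point, because the article names the levels explicitly and leaves out the home.

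**Conclusion.** The point holds in two parts. First, the stated clustering level and the described record coding do not match, and the Data Analysis Plan, Data Management and Ethical Considerations must be reconciled. Confidence that no HCP code exists is only moderate, because the chart is not shown. Second, whether or not such a code exists, a model of cases within HCPs has no nursing-home level although HCPs are nested in homes.

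The size rests wholly on assumed variance components. With HCPs linked across audits and 48 cases per home and period, type I error is about 16% at a home-by-period share of 2% and about 30% at 5%. It is about 11% and 19% if only half the cases are UTIs, and 5% if homes do not differ in their change. With unlinked codes it ran from about 1% to 10% in the case shown. This should be fixed; it does not by itself invalidate the study.

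**What to change.** - State which identifiers each record carries, so that the three sections agree.
- Make the nursing home the clustering level, with period (before or after) as the effect of interest, and add either a home-by-period random effect or standard errors clustered on the nursing home.
- If an anonymous HCP code exists, say so, say whether it is linked across the two audits, and fit cases within HCPs within homes. The HCP level need not be dropped.
- Country as a fixed effect is optional.

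The cost is analysis-plan wording. The home code is already on every chart and no new data are needed. Confidence intervals for the prescribing effect may widen.

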## Results

The local coordinators in each of the countries have already contacted all the nursing homes participating in the IMAGINE project, with a total of 109 nursing homes. All these nursing homes have already completed the first audit registration. The results of the first audit registrations will be available before the intervention takes place in November 2024. The overall results of the IMAGINE project will be available after summer 2025 and the results will be published by the end of 2025.

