The use of the Audit Project Odense method has certain limitations. The one notable weakness is the lack of external validity associated with the collected data. Since nursing home HCPs participate voluntarily, their prescribing habits may not accurately represent the average antibiotic use in all nursing homes within their country. Additionally, the nursing homes involved in the audits might exhibit a greater interest in quality improvement and potentially use more rational antibiotic practices compared to nonparticipating nursing homes [45]. Another aspect to consider is the potential influence of conducting an audit on providers’ prescribing behaviors. The HCPs are aware of being observed, which can lead to what is known as the Hawthorne effect. It is important to note that this study is not a clinical trial and lacks a control group, which could be considered a limitation. However, the study will compare the same participants before and after the intervention. Participation in a quality improvement project can pose a barrier due to the required time commitment. While completing a registration takes less than 2 minutes, HCPs need to allocate time for educational courses and other planned activities associated with the intervention. Another weakness is the cross-sectional nature of the Audit Project Odense method. The variables included in the registration chart are aligned with the consultation process, and ideally, the decision to treat should follow the establishment of a diagnosis. However, in practice, diagnostic procedures and treatment decisions are often intertwined [46]. HCPs may determine whether to prescribe a medication concurrently or even prior to establishing a diagnosis. Consequently, clinicians may adjust the diagnosis to align with the treatment decision, potentially introducing a diagnostic misclassification bias. Nevertheless, this potential bias would impact the validity of the diagnosis both before and after the intervention, with minimal likelihood of influencing the intervention’s effectiveness. Due to time constraints in the registration process and limitations on the maximum number of columns in the Audit Project Odense chart, only the typical signs and symptoms of UTIs are collected. This may result in certain limitations, as nonbiomedical factors that could serve as powerful predictors of antibiotic prescriptions are not considered in this study. This restricts the definition of antibiotic appropriateness in our study, as it is based on the collected items in the registration charts.

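### The only clustered model nests cases within health care professionals, a level that cannot be formed from the identifiers the protocol describes, and it leaves out the nursing home

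*Protocol article*

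**What the plan says.** The Protocol article's Data Analysis Plan gives the main comparisons as simple tests: "We will apply the chi-square test to determine the frequencies and appropriateness of prescriptions before and after the intervention and Student *t* test", the latter on the count of hygiene elements. It then adds one model for inappropriate UTI prescriptions: "multilevel logistic regression models with 2 levels: cases and HCP participants, to allow for the fact that patients belonging to the same HCP" may be correlated. No nursing-home level is mentioned.

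Other sections describe how records are keyed:

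- Ethical Considerations: data are "coded in the template with the code of the nursing home and a consecutive number for each antibiotic treatment". The same section says "No personnel data are collected from either HCPs or patients".
- Data Management: "Nursing homes will be identified by a code". No code for the health care professional (HCP) is mentioned.
- Setting: each home has a team of four HCPs.
- Project Methodology and Results: the first audit ran from February to April 2024, and "All these nursing homes have already completed the first audit registration" (109 homes). The second is planned for February to April 2025.
- Discussion, on the lack of a control group: "However, the study will compare the same participants before and after the intervention".

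**The concern.** The model's second level is a person, while the described key identifies a home and a treatment. With four HCPs in a home, the home code does not show which of them a record belongs to, and nothing described links an HCP in 2024 to the same HCP in 2025. The baseline audit is complete, so an identifier that was not recorded then may not be recoverable.

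Reducing inappropriate antibiotic use for UTIs is one of the primary objectives under Aims. The multilevel model is the only stated analysis of it that allows for dependence between cases. If it cannot be run as written, the chi-square test is what remains in the article. The statement that the same participants are compared depends on the same missing link.

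**Working it through.** **1. Stated volume.** The Data Analysis Plan aims for 50 cases in each of at least 100 homes: 50 × 100 = 5000 per audit, which reproduces its figure. At 109 homes it would be 50 × 109 = 5450. The article states no power calculation and no intracluster correlation (ICC), so there is nothing further to reproduce.

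**2. Which levels can be formed.**

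| Level | Units | Described key |
|---|---|---|
| Case | about 5000 per audit | consecutive treatment number |
| HCP (level 2 of the model) | 100 × 4 = 400, or 109 × 4 = 436 | none described |
| Nursing home (not in the model) | 100 to 109 | home code |

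The level in the model has no described key, and the level with a key is not in the model.

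**3. If an HCP code does exist.** Four HCPs share one home's residents and local practice, and under Setting they go on to train their own colleagues. A model with cases and HCPs alone assumes that these four are independent of each other.

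**4. Illustration of what is ignored, one audit.** Design effect = 1 + (m − 1) × ICC. The ICCs are assumptions. The column for m = 25 assumes that half of the cases are urinary, taken from the share of nearly 50% that the Introduction cites from an outside survey. The HCP column assumes that all four HCPs register equally, so m = 5000 / 400 = 12.5 (and 5450 / 436 = 12.5).

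| Assumed ICC | Home, m = 50 | Effective n of 5000 | Home, m = 25 | HCP, m = 12.5 |
|---|---|---|---|---|
| 0.01 | 1.49 | 3356 | 1.24 | 1.115 |
| 0.05 | 3.45 | 1449 | 2.20 | 1.575 |
| 0.10 | 5.90 | 847 | 3.40 | 2.15 |
| 0.20 | 10.80 | 463 | 5.80 | 3.30 |

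If the correlation sits wholly at home level, allowing for it only within HCPs understates the single-audit standard error. At ICC 0.05 the factor is √(3.45 / 1.575) = 1.48.

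**5. The before-after comparison.** The figures in step 4 are for one audit and must not be carried over unchanged. Let c be the correlation between a home's effects in the two audits. The design effect for the difference is then 1 + (m − 1) × ICC − m × ICC × c. With m = 50 and ICC = 0.05:

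- c = 0 (effects unrelated across audits): 1 + 2.45 − 0 = 3.45
- c = 1 (effects perfectly stable): 1 + 2.45 − 2.50 = 0.95

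Stable differences between homes cancel. What inflates the variance is change that differs between homes, and neither the chi-square test nor an HCP-only random intercept accounts for that.

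**The case against.** The strongest reply is that the article never says the home code and treatment number are the only fields. The coding sentence sits under Ethical Considerations, where it explains why residents' consent is not needed, and it is not a list of chart fields. The chart template (Figure 2) and the instruction sheet are not shown. The remark that "No personnel data are collected from either HCPs or patients" probably means personal data, and a non-identifying registrant number would be compatible with that. The Data Analysis Plan gives the charts a purpose for the individual professional, and the Discussion speaks of the same participants. Both hint at some attribution to HCPs.

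This stands, and it rules out several stronger readings that a reader might infer:

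- *No HCP identifier exists, so the model can never be fitted.* The documents support only that none is described.
- *The baseline cannot be repaired.* Registration is complete, but the paper charts are kept in the homes. The article does not say whether they can still be traced to a registrant.
- *The person registering is often not the prescriber.* Setting says only that the team may draw on "doctors that can be external or working in the facility part-time". It gives no frequency.
- *No clustered analysis is possible.* The home code is recorded, so clustering by home is available.

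The reply does not remove the point. If there is no HCP code, the stated level cannot be formed. If there is one, the data descriptions are incomplete and the model still omits the home. The protocol text needs changing in either case. A fuller analysis plan may exist, but the conflict is between statements the article itself makes.

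**Conclusion.** The point holds in this form: with the identifiers the protocol describes, level 2 of its only clustered model cannot be formed, and if an undescribed HCP code exists, the two-level model treats colleagues in the same home as independent. As the article stands, the only other analysis of inappropriate UTI prescribing is a chi-square test that treats every course as independent.

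The first part rests on four HCPs per home and on the keys being as described. The second part needs no numerical assumption.

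The numerical effect cannot be fixed from the documents. At an assumed ICC of 0.05 with 50 cases per home, the variance of the before-after difference could be anywhere from 0.95 to 3.45 times what the chi-square test assumes. The single-audit design effects do not show that the planned test has a grossly inflated error rate. The ground for change is that the stated model and the described data do not match, for a primary outcome, and that the recorded home code provides a workable clustering unit.

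**What to change.** - **Data Analysis Plan:** make nursing home, identified by its recorded code, the clustering level for both audits, with standard errors clustered by home. A random intercept for home alone would not capture change that differs between homes, and the clustered standard errors do. They also cover correlation between HCPs in a home and between repeat courses of the same unidentified resident.
- **HCP level:** keep it, nested within home, only if a non-identifying HCP code is present in both audits. In that case, correct Data Management and Ethical Considerations to say that the code is recorded.
- **Discussion:** unless HCPs can be linked across the audits, state that the same nursing homes, and not the same participants, are compared.

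The cost is a few sentences. The home code is already recorded, so no new resident or staff data are needed. The second audit and the analysis still lie ahead in the article's timetable. If an HCP code does exist, the nested level keeps the information it carries.
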